# The HortONS study. Treatment of chronic cluster headache with transcutaneous electrical nerve stimulation and occipital nerve stimulation: study protocol for a prospective, investigator-initiated, double-blinded, randomized, placebo-controlled trial

**DOI:** 10.1186/s12883-023-03435-9

**Published:** 2023-10-21

**Keywords:** Chronic cluster headache, Headache, Occipital nerve stimulation, Neuromodulation, Transcutaneous electrical nerve stimulation, ONS, TENS

## Abstract

**Background:**

Chronic cluster headache (CCH) is a debilitating primary headache disorder. Occipital nerve stimulation (ONS) has shown the potential to reduce attack frequency, but the occipital paresthesia evoked by conventional (tonic) stimulation challenges a blinded comparison of active stimulation and placebo. Burst ONS offers paresthesia-free stimulation, enabling a blinded, placebo-controlled study.

Identification of a feasible preoperative test would help select the best candidates for implantation.

This study aims to explore ONS as a preventive treatment for CCH, comparing burst stimulation to tonic stimulation and placebo, and possibly identifying a potential preoperative predictor.

**Methods:**

An investigator-initiated, double-blinded, randomized, placebo-controlled trial is conducted, including 40 patients with CCH. Eligible patients complete a trial with the following elements: I) four weeks of baseline observation, II) 12 weeks of transcutaneous electrical nerve stimulation (TENS) of the occipital nerves, III) implantation of a full ONS system followed by 2 week grace period, IV) 12 weeks of blinded trial with 1:1 randomization to either placebo (deactivated ONS system) or burst (paresthesia-free) stimulation, and V) 12 weeks of tonic stimulation.

The primary outcomes are the reduction in headache attack frequency with TENS and ONS and treatment safety. Secondary outcomes are treatment efficacy of burst versus tonic ONS, the feasibility of TENS as a predictor for ONS outcome, reduction in headache pain intensity (numeric rating scale), reduction in background headache, the patient’s impression of change (PGIC), health-related quality of life (EuroQoL-5D), self-reported sleep quality, and symptoms of anxiety and depression (Hospital Anxiety and Depression Scale, HADS).

Data on headache attack characteristics are registered weekly. Data on patient-reported outcomes are assessed after each trial phase.

**Discussion:**

The study design allows a comparison between burst ONS and placebo in refractory CCH and enables a comparison of the efficacy of burst and tonic ONS. It will provide information about the effect of burst ONS and explore whether the addition of this stimulation paradigm may improve stimulation protocols.

TENS is evaluated as a feasible preoperative screening tool for ONS outcomes by comparing the effect of attack prevention of TENS and tonic ONS.

**Trial registration:**

The study is registered at Clinicaltrials.gov (trial registration number NCT05023460, registration date 07–27-2023).

## Background

### Cluster headache

Cluster headache (CH) is a primary headache disorder characterized by attacks of strictly unilateral intense intra- or periorbital pain that lasts 15–180 min and often occurs multiple times a day. These painful attacks are often accompanied by ipsilateral autonomic facial symptoms such as nasal congestion and tearing [1]. The lifetime prevalence is about 1:1000 people [2, 3], and often debuts before the age of 40, potentially reducing the ability to live a normal family life and negatively impacting the ability to work [4, 5].

The majority of patients have episodic cluster headache where the headache attacks occur in bouts of weeks to months followed by a period of remission. However, approximately 15–20% have chronic cluster headache (CCH) [6] where the patients have attacks year-round with no remission periods longer than three months [1].

The headache attacks may be shortened by the use of injectable or intranasal triptans or oxygen inhalation that can be effective abortive treatments [7, 8], whereas preventive medication such as verapamil or lithium may reduce the number and severity of attacks [9, 10]. However, patients with CCH seem to respond less to abortive treatment than patients with episodic cluster headache, and the overall effect of preventive treatment is only moderate [11]. In addition, a proportion of CCH patients are medically refractory and still suffering from frequent attacks despite relevant trials with preventive medical treatment [11, 12] either because of insufficient treatment effects or due to intolerable side effects. This leaves patients with refractory CCH without any sufficient medical treatment options.

### Occipital nerve stimulation

The International Neuromodulation Society defines therapeutic neuromodulation as “the alteration of nerve activity through targeted delivery of a stimulus, such as electrical stimulation or chemical agents, to specific neurological sites in the body” [13]. In electrical neuromodulation, the nervous system can be modulated by a weak electrical current delivered by an electrode implanted in or close to a nerve structure.

Studies have indicated that electrical stimulation of the occipital nerves can be used as a preventive treatment for refractory CCH with the potential to significantly reduce the frequency of headache attacks and—to some extent—also the pain intensity [14–19]. Occipital nerve stimulation (ONS) is an invasive but non-destructive procedure where one or two leads for electrical stimulation are permanently implanted subcutaneously across the greater occipital nerves (GON). The lead(s) is connected to an implantable pulse generator (IPG) that produces the electrical pulses for the stimulation. Depending on the surgical technique, the IPG is typically placed subcutaneously in the gluteal or sub-clavicular region.

The electrical pulses used in conventional (“tonic”) ONS evoke perceptible occipital paresthesia which challenges blinded comparison with placebo, but open-label studies find that approximately two-thirds of patients treated with ONS experience a reduction in attack frequency of 50% or more [10–15], markedly improving the patients quality of life [20]. Importantly, the therapeutic effect seems to be long-term [21, 22]. To our knowledge, only one large blinded, randomized trial on ONS for CCH has been published, exploring a dose–response relationship between ONS efficacy and stimulation intensity [23].

A novel stimulation paradigm termed burst stimulation, originally designed for spinal cord stimulation for chronic neuropathic pain, has given rise to paresthesia-free stimulation [24]. The scientific evidence on burst stimulation used for ONS is scarce, but in two small studies, it has been suggested that paresthesia-free burst stimulation may have a similar effect as tonic ONS reducing attack frequency in CCH patients [25, 26].

### Preoperative screening

Not all patients with CCH treated with ONS seem to experience sufficient if any, effect of ONS treatment [23]. Currently, no well-documented predictor for ONS outcome is known. Because of the invasive nature of the treatment, and the fact that ONS is characterized by high initial device costs, it would be favorable to have a reliable screening tool to help select the best candidates for implantation and avoid operating on patients who are unlikely to benefit from the ONS treatment.

It has been investigated if a previous good clinical response to interim treatment with prednisolone and/or a local anesthetic injected around the GON (i.e., a GON block) could predict ONS outcome, but without convincing results [27, 28]. Also, no specific clinical phenotypes that can distinguish which CCH patients are most likely treatment responders from non-responders have yet been identified.

In a small study, it has been suggested that non-invasive external transcutaneous electrical nerve stimulation (TENS) of the GON could be a possible predictor for ONS outcome [29], but it remains to be systematically explored whether TENS is a feasible preoperative screening tool.

The purpose of this study is to validate the efficacy and safety of ONS as a treatment for CCH and to explore whether burst ONS is as effective as headache attack prevention as conventional tonic ONS. In addition, we wish to investigate whether TENS of the greater occipital nerves (GON) can be used as a predictor of the effect of surgical treatment with ONS for CCH.

## Methods: Participants, interventions, and outcomes

### Study design

The study is an investigator-initiated, prospective, double-blinded, randomized, placebo-controlled trial.

After an initial baseline period, all participants are treated with TENS. Following the TENS trial all participants are implanted with an ONS system and randomized into one of two arms; one intervention arm and one placebo arm with an allocation ratio of 1:1. The participants in the intervention arm receive burst ONS (paresthesia-free stimulation). In the placebo group, the ONS system will be left turned off. In the final trial phase, all participants cross over to open-label tonic ONS (Fig. 1).

**Fig. 1 Fig1:**
[figure not shown]
Study flowchart. TENS, transcutaneous electrical nerve stimulation. ONS, occipital nerve stimulation

### Study setting

Patient recruitment and follow-up are carried out at the Department of Neurosurgery, Aarhus University Hospital, and the Danish Headache Centre, Rigshospitalet-Glostrup, University of Copenhagen, Denmark.

All ONS implantations and surgical follow-up visits are performed at the Department of Neurosurgery at Aarhus University Hospital, Denmark.

### Eligibility criteria

A total of 40 patients with CCH will be included in the study and have a full ONS system implanted. The diagnosis is confirmed after a thorough neurological assessment based on the criteria listed in the *International Classification of Headache Disorders, 3. Edition (ICHD-3)* [1], see Table 1 and Table 2.

**Table 1 Tab1:** Diagnostic criteria for cluster headache

A. At least five attacks fulfilling criteria B-D
B. Severe or very severe unilateral orbital, supraorbital, and/or temporal pain lasting 15–180 min (when untreated)
C. Either or both of the following
1. At least one of the following symptoms or signs, ipsilateral to the headache:
• Conjunctival injection and/or lacrimation
• Nasal congestion and/or rhinorrhea
• Eyelid edema
• Forehead and facial sweating
• Miosis and/or ptosis
2. A sense of restlessness or agitation
D. Occurring with a frequency between one every other day and 8 per day
E. Not better accounted for by another ICHD-3 diagnosis

**Table 2 Tab2:** Chronic cluster headache

A. Attacks fulfilling criteria A-E for Cluster headache, and criterion B below
B. Occurring without a remission period, or with remissions lasting < 3 months, for at least one year

*ICHD-3* International classification of headache disorders 3^rd^ edition

In addition to meeting the ICHD-3 criteria for CCH, participants must also comply with the study eligibility criteria listed in Table 3.

**Table 3 Tab3:** Eligibility criteria

**Inclusion criteria**
• Age of 18 years and above
• Signed informed written consent
• Chronic cluster headache with ≥ 15 attacks per month
• Stable use of preventive cluster headache medication 30 days prior to study enrollment
**Exclusion criteria**
• Other ongoing neuromodulation therapies
• Current alcohol and/or drug abuse
• Known severe psychiatric disorders
• A concomitant second type of chronic primary or chronic secondary headache (e.g., chronic migraine or chronic post-traumatic headache, while chronic tension-type headache is allowed)
• Major posterior cervical surgery at C3-level and above
• Pregnancy
• Treatment with oral steroids and/or GON block 30 days before study enrollment

During the trial, the participants may continue their usual preventive and abortive headache medication, but they cannot have any dose increase of their current medication or start new preventive medication. Neither can the participants receive any interim treatment such as GON blocks (with injected steroids and/or local anesthetics) or high-dose oral prednisolone after enrollment. In this case, the participant will be withdrawn from the study. A reduction in medicine dose or discontinuation of a drug is allowed.

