### European Quality of Life – 5 Dimensions (EuroQoL-5D)

EuroQoL-5D is a standardized tool for examining the health-related quality of life, and consists of a descriptive part with five questions about mobility, personal care, usual activities, pain, and anxiety/depression. In addition, the questionnaire also contains the EQ-VAS (visual analog scale), which measures the participant's self-assessed state of health on a 0–100 scale from "worst imaginable" to "best imaginable" [33].

In this study, the participants fill out the EuroQoL-5D questionnaire at the end of each trial phase (baseline, TENS trial, blinded trial, and tonic ONS trial).

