### Sample size

Based on our previous experience with ONS treatment [26], we estimate that 50% of the participants who receive active treatment with burst ONS will reach the primary endpoint of a 30% reduction in attack frequency. A blinded trial with burst ONS and placebo has to our knowledge not been carried out earlier, but we hypothesize that no more than 10% in the placebo group will meet the primary endpoint [35]. The sample size is calculated using Fisher’s Exact test based on the above-mentioned assumptions and with 80% power (two-tailed) and a α = 0.05, a total of 40 participants (20 in each allocation group) are needed to be enrolled in the study and an ONS-system implanted.

Each enrolled participant contributes their data regardless of whether they complete the project or not. In case of participants excluded after enrollment, the reason for exclusion will be described.

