### Statistical analysis

Statistical analysis will be conducted by the principal investigator and a statistician blinded for treatment allocation only after follow-up for all participants is completed. No interim analysis will be performed.

Characteristics of the patients will be presented using descriptive statistics to assess if balanced groups were obtained after randomization. The primary analysis will be conducted according to the intention-to-treat principle to avoid introducing bias. In a secondary analysis, a per-protocol analysis will be performed.

The primary outcome is a 30% reduction in attack frequency with TENS and ONS treatment compared to baseline. Relative change in attack frequency (in percent) will be analyzed using the Wilcoxon signed-rank test for paired variables, comparing the baseline data with data from the TENS trial and the trial with burst and tonic ONS, respectively. Because the changes in attack frequency are expectedly skewed [23], a non-parametric test will be applied. In cases with a minimum 30% reduction in attack frequency, sub-analyses will be made to group the treatment responders after relevant cutoffs.

Analysis of the secondary outcomes will be conducted according to the same principle, comparing data from each of the trial phases to baseline using a parametric or non-parametric test for paired variables, depending on the data distribution.

The feasibility of TENS as a predictor for ONS outcome will be evaluated by determining the sensitivity and specificity and calculating the predictive values.

Statistical data analysis will be performed using Stata 17.0 (StataCorp, College Station, USA-TX).

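### Withdrawing a participant from the whole trial after a prohibited GON block or prednisolone course ends outcome collection, and after randomisation this weakens the intention-to-treat analysis

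*Protocol article*

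**What the plan says.** The rule stands in the protocol article under Eligibility criteria, in the paragraph after the exclusion criteria of Table 3. Usual preventive and abortive drugs may continue, but dose increases and new preventives are barred. The text goes on: "Neither can the participants receive any interim treatment such as GON blocks (with injected steroids and/or local anesthetics) or high-dose oral prednisolone after enrollment". The consequence follows directly: "In this case, the participant will be withdrawn from the study".

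Two sentences under Sample size bear on what happens next: "Each enrolled participant contributes their data regardless of whether they complete the project or not", and "In case of participants excluded after enrollment, the reason for exclusion will be described".

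Under Statistical analysis, "The primary analysis will be conducted according to the intention-to-treat principle to avoid introducing bias". The same paragraph adds: "In a secondary analysis, a per-protocol analysis will be performed".

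The phases run in sequence. After the blinded comparison of burst stimulation with a switched-off device, the Study design section says: "In the final trial phase, all participants cross over to open-label tonic ONS". Quality of life is tied to the phases, since "the participants fill out the EuroQoL-5D questionnaire at the end of each trial phase"; HADS follows the same schedule, and PGIC is recorded for each treatment. According to the Discussion, TENS is judged as a screening tool by comparing its effect with that of tonic stimulation.

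**The concern.** The plan promises an intention-to-treat primary analysis, yet one of its own rules stops outcome collection in participants who take a prohibited rescue treatment. The banned treatments are used for uncontrolled attacks, so receiving one plausibly marks a participant who is doing badly. If so, the missing outcomes are related to the outcome itself. An analysis plan can choose how to treat missing values, but it cannot recover observations that the protocol stopped collecting.

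The plan already has a suitable place to exclude such participants, namely the per-protocol analysis. Removing them from the trial as well gains nothing for that analysis and takes information from the primary one. At stake are the completeness of blinded-phase follow-up, the end-of-phase questionnaires, and the tonic-phase result that serves as the reference for TENS as a predictor. Only 40 participants are planned, each with an implanted system.

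**Working it through.** The plan gives no figure on this point to reproduce: it states no expected number or rate of withdrawals. The check is a reading of the sections together, followed by a count of what one withdrawal costs.

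**Sections side by side.**
- Eligibility criteria: the participant leaves the trial. The text does not limit this to treatment or to an analysis set.
- Sample size: non-completers still contribute data, and the reason for an exclusion is reported. The natural reading is that data in hand are kept. Neither sentence provides for further collection.
- Statistical analysis: intention-to-treat is primary. This settles who is analysed and in which group; it does not create outcomes that were never recorded.

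**Timeline** (Abstract, Methods). Baseline 4, TENS 12, grace period 2, blinded phase 12 and tonic phase 12 weeks: 4 + 12 + 2 + 12 + 12 = 42 weeks. Randomisation comes after 4 + 12 + 2 = 18 weeks, leaving 24. A withdrawal in the first 18 weeks does not bear on burst versus placebo, although it does take data from the TENS analyses.

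**Loss per withdrawal.** If rescue follows blinded week w, the registrations lost are (12 − w) + 12:
- w = 3: 9 + 12 = 21 of 24
- w = 6: 6 + 12 = 18 of 24
- w = 9: 3 + 12 = 15 of 24

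EuroQoL-5D and HADS are completed at baseline and after the TENS, blinded and tonic phases, so 2 of 4 rounds are lost, together with PGIC for the same two phases. Rescue in the tonic phase after week w loses 12 − w registrations and 1 of 4 rounds.

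**What analysis rules can and cannot repair.** Counting a rescued participant as a non-responder settles the 30% endpoint for that phase without more data. It does not supply PGIC, EuroQoL-5D or HADS at the end of the phase. Nor does it supply the tonic phase, so the participant has no tonic value for the paired comparison with baseline and no reference result for the sensitivity and specificity of TENS.

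**Direction.** Take the planning rates under Sample size (10 of 20 responders on burst, 2 of 20 on placebo: a 40-point difference) and suppose, purely for illustration, that 10% of the non-responders in one arm are left out.
- Placebo only: 10/20 − 2/(2 + 18 × 0.9) = 0.500 − 2/18.2 = 0.500 − 0.110 = 0.390
- Burst only: 10/(10 + 10 × 0.9) − 2/20 = 10/19 − 0.100 = 0.526 − 0.100 = 0.426

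The difference moves down or up by less than 3 points depending on which arm loses participants. The 10% is an assumption, and leaving participants out is not what the plan describes. The example shows only that no direction can be assigned.

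**The case against.** The best case for the plan has four parts.

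First, this is a condensed article, and follow-up after withdrawal could be set out in the full protocol. That would carry weight if the article were silent. It is not: it states a consequence, and the consequence is withdrawal from the trial. How rescued participants are counted is analysis-plan material; whether their outcomes are still collected depends on this rule.

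Second, every enrolled participant contributes data and the primary analysis is by intention to treat. A reader might infer that rescued participants drop out of the analysis, that response rates are inflated, or that burst versus placebo loses power. The documents do not support this. Leaving people out would contradict both the Sample size and the Statistical analysis sections. Fisher's exact test is named only for the sample size, while the stated primary analysis is a within-participant signed-rank test. No bias in that test has been shown. This part of the objection stands in full.

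Third, attack counts after a GON block or prednisolone are affected by that treatment, so not all the lost registrations are equally useful. A rescue late in the blinded phase could also carry over into the first tonic weeks. This stands too. It is a reason to flag such data, not to leave them uncollected, and it applies less to late tonic weeks.

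Fourth, withdrawal is sensible early in the trial. A rescue during baseline or TENS would distort the reference for every later comparison, and continuing would take that participant on to implantation. This stands and limits the fix to rescue after randomisation.

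That rescued participants are doing badly remains an inference, though a reasonable one.

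**Conclusion.** The point holds as a weakness in a stated rule. After randomisation, withdrawal from the trial stops outcome collection in participants who plausibly have poor headache control, and so works against the intention-to-treat analysis that the plan makes primary. Per participant the loss is substantial: 15 to 21 of 24 registrations for rescue between blinded weeks 9 and 3, two questionnaire rounds, and the tonic reference for TENS. Across the trial its size and direction are unknown, because the article gives no withdrawal rate and only specific treatments trigger the rule.

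The conclusion assumes that withdrawal means no further registrations or questionnaires, and that rescue is related to headache control. It reads the trigger narrowly, as the two interim treatments; if the sentence also covers dose increases and new preventives, more participants are affected.

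This is a cheap improvement of minor to moderate severity.

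**What to change.** Keep the ban. Keep withdrawal for rescue before randomisation (baseline, TENS and grace period), where it protects the baseline and TENS reference.

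For rescue after randomisation, replace the sentence "In this case, the participant will be withdrawn from the study" with a rule to this effect:
- the treatment is recorded as a protocol deviation;
- weekly registrations, questionnaires and the planned tonic phase continue;
- the participant stays in the randomised group for the intention-to-treat analysis;
- rescue counts as non-response on the 30% endpoint for the phase in which it occurs;
- the participant is excluded from the per-protocol analysis only.

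For anyone already withdrawn after randomisation, keep the data up to withdrawal and apply the same non-responder rule.

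The cost is a short amendment and continued follow-up of probably few participants, through e-mailed forms that already exist. Response rates may come out slightly lower. Attack counts after rescue, including early tonic weeks after a late blinded-phase rescue, are affected by the rescue drug; they should be flagged and examined in a sensitivity analysis.

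Continued collection helps only participants still in follow-up. Recruitment was expected to end in late 2023; if the last participant enrolled then, 42 weeks of follow-up would run to about October 2024, a year after publication.
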